## Summary

**Background:** By expanding primary health care services, Ethiopia has reduced under-five mortality. Utilisation of these services is still low, and concerted efforts are needed for continued improvements in newborn and child survival. “Optimizing the Health Extension Program” is a complex intervention based on a logic framework developed from an analysis of barriers to the utilisation of primary child health services. This intervention includes innovative components to engage the community, strengthen the capacity of primary health care workers, and reinforce the local ownership and accountability of the primary child health services. This paper presents a protocol for the process and outcome evaluation, using a pragmatic trial design including before-and-after assessments in both intervention and comparison areas across four Ethiopian regions. The study has an integrated research capacity building initiative, including ten Ph.D. students recruited from Ethiopian Regional Health Bureaux and universities.

**Methods:** Baseline and endline surveys two years apart include household, facility, health worker, and district health office modules in intervention and comparison areas across Amhara, Southern Nations Nationalities and Peoples (SNNP), Oromia, and Tigray regions. The effectiveness of the intervention on the seeking and receiving of appropriate care will be estimated by difference-in-differences analysis, adjusting for clustering and for relevant confounders. The process evaluation follows the guidelines of the UK Medical Research Council. The implementation is monitored using data that we anticipate will be used to describe the fidelity, reach, dose, contextual factors and cost. The participating Ph.D. students plan to perform in-depth analyses on different topics including equity, referral, newborn care practices, quality-of-care, geographic differences, and other process evaluation components.

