## Design and methods

### Setting

The Federal Ministry of Health in collaboration with the non-governmental partners UNICEF, Last 10 Kilometres/John Snow, Inc., Save the Children, and PATH initiated the “Optimizing the Health Extension Program” project to increase the utilisation of primary child health services. This evaluation has a pragmatic trial design with purposefully selected 26 intervention and 26 comparison districts (woredas), with a total population of 8 million, across four regions of Ethiopia (Amhara, Southern Nations Nationalities and People, Oromia, and Tigray). Figure 1 shows the intervention and comparison areas within these four regions.

[figure not shown]

Figure 1. Map of Ethiopia showing all regions (left) and the intervention and comparison districts within the four study regions (right).

The intervention areas are selected by government and implementing partners for having a relatively low utilization of primary child health services. The Regional Health Bureaus in these regions, with the support from their local universities, will select the comparison districts to match the intervention districts. Selection is based on demographic and health criteria that includ population size, number of primary health care units, burden of diseases, health service performance data, length of time since iCCM and CBNC program initiation, prior exposure to other similar programs, and absence of non-governmental organizations addressing demand generation. The intervention, which will start in 2016, has an intended duration of 2.5 years and is based on an analysis of barriers to the utilisation of newborn, child and maternal health services. The planned evaluation follows a plausibility approach (16). It includes analysis of difference in differences of outcomes and a process evaluation of the intervention in line with the UK Medical Research Council’s guidelines (17).

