### The intervention and underlying assumptions

The package of interventions to be implemented across 26 districts includes three interlinked strategies with possible synergies: (1) community engagement activities that aim at increasing the awareness of newborn and child diseases, the recognition and acceptance of the care provided on the primary level, and the formulation of action plans at the local level; (2) capacity building of HEWs and WDA leaders such as gap filling training, supportive supervision and mentorship to improve iCCM and CBNC services, and (3) strengthening the local government’s ownership and accountability of the primary newborn and child health services by advocating for the sustained integration of CBNC and iCCM into the planning, budgeting, monitoring, management and support systems of the district and sub-district level (Table 1). Assumptions made by the implementers to achieve the success of the Optimizing the Health Extension Program included support from local stakeholders, traditional and religious leaders, governmental health sector and supply chain partners.

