### Outcomes

*The primary outcome* is care seeking (at health posts, health centres, hospitals and clinics) for an illness in under-fives. *Secondary outcomes* include appropriate treatment for diarrhoeal diseases (oral rehydration therapy, zinc tablets), probable pneumonia (antibiotics), fever and malaria, and neonatal sepsis (antibiotics); improved knowledge towards childhood illnesses and treatment services among caregivers of under-5 children; improved attitudes or perceptions towards the iCCM and CBNC services at health posts; improved iCCM and CBNC program ownership by the public health sector (including inclusion of iCCM and CBNC indicators in their planning and budget allocation); and, improved availability of quality iCCM services provided by the HEWs.

*The sample size* for baseline and endline surveys is based on the requirement that these surveys should have adequate power to measure changes in a fixed number of percentage points between intervention and comparison areas from start to end of the study. For the household survey, the sample size was powered for the main outcome of care seeking for any illness in the two weeks prior to the survey. Sampling 30 households in the 100 selected enumeration areas would yield 3000 households per group. The Ethiopia Demographic Heath Survey (DHS) data has shown that the rate of children under-five to households surveyed was 0.65. Based on this assumption, a sample survey of 3000 households per group would be expected to achieve a sample size of 1747 children below the age of five years. The evaluation of the integrated management of childhood illness in Tanzania reported 50% of under-five children to have had an illness in the two weeks prior to the survey (28). We assumed a more conservative 30%. Based on the calculations of a sample size of 3000 households per group (6000 in total) with 90% completeness and a design effect of 1.3, we would have 80% power to detect differences of 10-20 percentage points across the range of child health indicators as statistically significant at the 5% level.

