*The baseline and endline surveys* will be conducted in intervention and comparison areas to assess the situation before the intervention. A two-stage stratified cluster sampling will be applied in these two surveys using lists of enumeration areas of the 52 intervention and comparison districts from the latest (2007) Ethiopian census as the sampling frame. In the first stage, a list of all enumeration areas of the study districts will be based on the 2007 Ethiopian Housing and Population Census. Two hundred enumeration areas will be selected from 52 districts with probability proportional to size. Each enumeration area will form one cluster, and these clusters will constitute the primary sampling unit. In the second stage, a systematic random sampling technique will be applied to select 30 households in each cluster. All women aged 13 to 49 years who live in the selected households will be included, in order to identify women who had a live birth in the 12 months prior to the survey to assess care seeking in the neonatal period. Furthermore, children under the age of 5 years will be included to assess care seeking for any illness in the two weeks prior to the survey. For every cluster, the WDA leader serving the cluster will be interviewed. The health post and the HEWs serving the selected cluster, the health post’s referral health centre, and staff, and the district health office providing support to the selected facility will be approached with survey modules. All study participants will be sampled without replacement. Up to three visits will be made to each participant to maximize their inclusion into the study.

To evaluate the quality of assessment and care provided to sick children at the health posts, an observation of a sick child consultation with an HEW and a re-examination by a child health officer will be performed. Given that very few sick children are brought to the health post each day, data collectors will mobiliz the community to bring sick children on the day of the survey to ensure the required sample size is met.

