Data collection teams and supervisors will be trained over the course of ten days. They will not be provided information on whether a district is an intervention or comparison area. Data will be collected on tablets and encrypted data will be regularly sent from the field to the Ethiopian Public Health Institute’s central server. The data manager will then decrypt the data and rigorous quality checks will be conducted with feedback to the field teams. Data cleaning will involve checking for errors, completeness and consistency. The data manager will also ensure that all standards for data security, curation and access were met.

*The effectiveness assessment* will be based on a plausibility design (16), analysing difference-in-differences of the primary and secondary outcomes (31). Data on primary and secondary outcomes will be analysed from baseline and endline household, health post, and health centre surveys in intervention and comparison districts, with adjustment for the cluster sampling and relevant confounding factors. The assessment will use blinded analysis. The code identifying the intervention and comparison areas will be revealed after the analysis and interpretations are completed.

Ten Ph.D. students from four Ethiopian universities, including candidates from the Regional Health Bureaus in the study provinces, and from the Ethiopian Public Health Institute, are engaged in the evaluation. PhD students will be involved in the conduct of the surveys, participating in the training of data collectors and serving as regional survey coordinators. They have chosen topics for in-depth sub-studies linked to the evaluation, including equity in the utilisation of services; spatial analyses of care utilisation; quality of care provided by the HEWs; the role of WDA leaders in promoting the use of services; newborn care practices; the referral of sick children; and focused studies of care utilisation for diseases of the newborn and diarrhoeal diseases. Most of the students plan to use baseline and endline surveys for quantitative data and to perform qualitative studies within their chosen topics.

Findings from the effectiveness study, process evaluation and PhD research will be published as scientific articles and reports. No professional writers will be used. Publications arising from this evaluation will follow the recommendations from the International Committee of Medical Journal Editors (32).

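### The intervention is assigned by district, but the protocol defines clusters as enumeration areas and adjusts only for the cluster sampling, so the standard errors may be wrong in either direction

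*Protocol*

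**What the plan says.** **Assignment.** The Setting section describes "purposefully selected 26 intervention and 26 comparison districts (woredas", the comparison districts being chosen to match. The section on the intervention and its assumptions confirms the level: "The package of interventions to be implemented across 26 districts includes three interlinked strategies with possible synergies". Part of the package (district planning and budgeting, advocacy workshops, radio) operates above the enumeration area.

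**Sampling.** In Outcomes, the paragraph on the surveys states: "Two hundred enumeration areas will be selected from 52 districts with probability proportional to size". It continues: "Each enumeration area will form one cluster, and these clusters will constitute the primary sampling unit".

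**Analysis.** In Outcomes, the paragraph on the effectiveness assessment sets out a DiD on primary and secondary outcomes "with adjustment for the cluster sampling and relevant confounding factors". The Summary says that effects will be "estimated by difference-in-differences analysis, adjusting for clustering and for relevant confounders". Neither names a level other than the one that the sampling text defines.

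**Sample size.** In Outcomes: "Sampling 30 households in the 100 selected enumeration areas would yield 3000 households per group". The power statement is made "with 90% completeness and a design effect of 1.3", without an ICC, a cluster size or a level.

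**The concern.** The independent units for an intervention effect are the units that receive or do not receive the intervention. Here these are 52 districts, with 200/52 = 3.85 sampled enumeration areas in each on average. Areas of one district share its managers, supply chain, supervision and local events. The protocol expects such influences: the district questionnaire asks about epidemics and disasters, and the barrier analysis lists stock-outs and uneven supervision.

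A DiD removes whatever is constant in a district across rounds, but not what changes. If district-level changes exist and the standard error treats 100 areas per group as independent, a change in a few districts can look more certain than it is. Assignment was purposive, so the evaluation cannot fall back on randomisation, and the findings are meant to inform national scale-up. The width of the primary interval therefore matters.

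**Working it through.** **Inputs from the protocol (Outcomes and Setting).** 3000 households per group and survey round; 0.65 under-fives per household; 90% completeness; 1747 children per group; 30% ill in the past two weeks; design effect 1.3; 80% power; 5% level (two-sided assumed); 100 areas and 26 districts per group.

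**Step 1: the plan's own figures.**
- Children: 3000 × 0.65 × 0.90 = 1755, against 1747 stated.
- Ill children per group per round: 1747 × 0.30 = 524.1. Effective number: 524.1/1.3 = 403.
- With 403 per group, a single-round comparison detects 9.9 points at base rates of 40% to 50%. A DiD detects about 13 to 14 points at base rates of 30% to 50%. The stated 10 to 20 points is reproduced.

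**Step 2: the level that 1.3 fits.**
- Ill children per area: m = 524.1/100 = 5.24. Per district: 524.1/26 = 20.16.
- At area level, 1.3 implies an ICC of 0.3/(5.24 − 1) = 0.071. Applied to whole districts, that ICC would give 1 + 19.16 × 0.071 = 2.36.
- At district level, 1.3 would imply an ICC of 0.3/(20.16 − 1) = 0.016.
- Both readings are arithmetically possible. The area reading agrees with the protocol's definition of a cluster, but it remains an inference. Steps 3 and 4 use it.

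**Step 3: district-by-round variation (ρ_D, assumed).** Areas per district: k = 100/26 = 3.85.
- True design effect: DE = 1.3 + m(k − 1)ρ_D = 1.3 + 14.92ρ_D.
- True type I error of an area-clustered 5% test: 2[1 − Φ(1.96 × √(1.3/DE))].
- Detectable DiD at 80% power, with variance 0.25 in each of the four cells: (1.960 + 0.842) × √(4 × 0.25 × DE/524.1).

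| ρ_D | DE | Type I error | Detectable DiD (points) |
|---|---|---|---|
| 0 | 1.30 | 5.0% | 14.0 |
| 0.01 | 1.45 | 6.3% | 14.7 |
| 0.02 | 1.60 | 7.7% | 15.5 |
| 0.04 | 1.90 | 10.5% | 16.9 |

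**Step 4: stable district differences (ρ_S, assumed).** These cancel in the DiD. Standard errors that treat the areas of the two rounds as separate clusters still count them. The true design effect is then 1.3 − 5.24ρ_S:
- ρ_S = 0.01: DE 1.25, type I error 4.5%.
- ρ_S = 0.03: DE 1.14, type I error 3.7%.
- ρ_S = 0.05: DE 1.04, type I error 2.8%.

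**Step 5: both together.** DE = 1.3 − 5.24ρ_S + 14.92ρ_D. With ρ_S = 0.03 and ρ_D = 0.01, DE = 1.3 − 0.157 + 0.149 = 1.29, and the type I error is about 5%. The net direction depends on two quantities that the documents do not give.

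**The case against.** The sentence that defines the cluster describes sampling, and for the design as described the enumeration area is the correct primary sampling unit. The analysis wording does not exclude a district term. The Summary's version is broader still, and the level of the standard errors is often left to a statistical analysis plan, which is not shown. District shocks are also partly covered by the district questionnaire, the confounder adjustment and the process evaluation.

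Some of this stands: the text does not forbid district-level inference, and a later document may supply it. But the protocol is not merely silent. It fixes one definition of a cluster, ties the adjustment to the cluster sampling, and bases a power claim on a design effect. Followed as written, it leads to area-level errors. Adjusting for measured confounders does not make areas of one district independent.

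A reader might infer that the false-positive rate does exceed 5%. The documents do not support this as a fact. It requires an analysis that ignores district and a district-by-round correlation that is not outweighed by stable differences. No such correlation is given, and steps 4 and 5 show that the error can be below or near 5%. A reader might also infer that the power claim fails, but 14.7 to 16.9 points lies within the stated 10 to 20. Finally, it is not established that 1.3 omits district correlation, because its level is not stated.

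**Conclusion.** The mismatch holds: assignment is by district, the only defined cluster is the enumeration area, and nothing in the sample-size or analysis text provides for correlation between areas of one district. The consequence is conditional. With a district-by-round correlation of 0.01 to 0.04, no offsetting stable component, 1.3 read as an area-level design effect and an analysis clustered on areas only, the type I error is about 6% to 11%. If district differences are stable and the rounds' areas are treated as separate clusters, the test is somewhat conservative, at about 3% to 4.5% for stable correlations of 0.01 to 0.05. All these correlations are assumptions. What can be said firmly is that the standard errors as described do not match the unit of assignment, so the primary interval's coverage is not assured in either direction.

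**What to change.** In the effectiveness-assessment paragraph of Outcomes, replace the reference to cluster sampling with inference at district level, and keep the confounder adjustment. Either of two forms would do:
- standard errors clustered on the 52 districts across both rounds, with a small-sample correction; or
- a model with district and district-by-round random effects and enumeration area nested within district.

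Both let stable district differences cancel and count those that change, so they correct the error whichever way it runs.

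In the sample-size paragraph, state the ICC and the clustering level behind the 1.3 design effect, and allow for a district-by-round component.

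District fixed effects, matched-set terms and region-by-round terms are optional and not part of this correction. The protocol defines no matched pairs or sets on which a matched term could be built.

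The cost is a change of wording and a small change to the model code. No new data are needed. Intervals may become somewhat wider: the small-sample correction alone, with about 50 degrees of freedom, moves the critical value from 1.960 to 2.009, a factor of 2.009/1.960 = 1.025.

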For the survey to assess the quality care provided by HEWs, with the assumption that each of the sampled enumeration areas will be served by one health post, the survey will include 100 intervention and 100 comparison area health posts for the quality of care assessment, where in each health post, the HEWs’ assessment of four sick children mobilized to come to the health post will be observed, followed by a re-examination of the child by a health officer. This will yield a sample size of 400 children in each group. A total of 800 children, with a design effect of 1.4, will have 80% power to detect a minimum of 15 percentage point changes in the correct classification of iCCM illnesses between intervention and comparison area HEWs at baseline and endline as statistically significant at the 5% level.

*The questionnaire tools for baseline and endline surveys* were adapted from the team’s own, and others’ previous work on the Integrated Management of Childhood Illness (28), iCCM (29), and CBNC (30). The questionnaire instrument includes modules regarding household, health posts and health centres, HEWs, health centre staff, WDA members, an observation and re-examination of the HEW assessing sick children, and district contextual factors (Table 2).

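### The survey can add to its own primary outcome: sick children are mobilised to the health post in the sampled clusters, household interviews are not required to come first, and prompted visits are not excluded

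*Protocol*

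**What the plan says.** All of the relevant text is in the Outcomes section of the protocol.

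- The primary outcome "is care seeking (at health posts, health centres, hospitals and clinics) for an illness in under-fives". A health-post visit is therefore an outcome event.
- In the household survey, "children under the age of 5 years will be included to assess care seeking for any illness in the two weeks prior to the survey".
- The quality-of-care sample is tied to the same clusters, "with the assumption that each of the sampled enumeration areas will be served by one health post". At each health post the health extension workers' "assessment of four sick children mobilized to come to the health post will be observed". The protocol adds: "This will yield a sample size of 400 children in each group".
- The reason for mobilising is stated: "Given that very few sick children are brought to the health post each day". Hence "data collectors will mobiliz the community to bring sick children on the day of the survey to ensure the required sample size is met".
- Each participant may be approached as many as three times, so household work in a cluster need not be finished in one pass.

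The section sets no order between household interviews and mobilisation. It does not limit mobilisation to households outside the sample of 30, and it has no rule for a visit that the survey team prompted.

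**The concern.** One part of the survey produces health-post visits and another part, in the same places, counts them. A mother who brings a sick child because the team asked, and who is interviewed or revisited on a later day, truthfully reports a health-post visit for illness within the recall window. It is recorded as care seeking although the family might not have sought care otherwise.

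The problem cannot be repaired at analysis unless field order, visit date or prompting was recorded. Contamination that is equal in all four group-by-round cells raises the measured level of care seeking and pulls the difference-in-differences towards zero. Contamination that differs by area and round would bias the estimate directly. Treatment outcomes reported in the household module are exposed in the same way, because a prompted child is also assessed at the health post.

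**Working it through.** **Inputs from the protocol (Outcomes):** 30 households in each of 100 enumeration areas per group; 0.65 under-fives per household; 90% completeness; 1747 under-fives per group; 30% ill in the past two weeks; four mobilised children per health post; detectable differences of 10 to 20 percentage points.

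**Assumptions not in the protocol:** households served per health post, H = 150 to 1000; share of household interviews held after mobilisation, f = 1 unless stated; true care seeking, p = 30%, used only to show levels. Mobilised children are taken to be spread evenly over the H households, and to be no more and no less likely than other ill children to have sought care anyway.

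**Step 1, the plan's own figure.** 3000 × 0.65 × 0.90 = 1755 under-fives per group, against 1747 stated. The difference is 8 children (0.5%), so the figure reproduces.

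**Step 2, size of the outcome denominator.** 1747 × 0.30 = 524 ill children per group, or 524/100 = 5.24 per cluster.

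**Step 3, prompted visits.** 4 × 100 = 400 per group per round. Only those from sampled households can enter the outcome. If all four children lived in the 30 sampled households, the share would be 4/5.24 = 76%. That is a ceiling, not an estimate.

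**Step 4, share of ill sampled children affected.** c = f × 4 × (30/H) / 5.24.

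**Step 5, effect on the estimate.** The observed proportion is p + c(1 − p). With the same c in all four cells, the observed difference-in-differences is the true value × (1 − c).

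| H (assumed) | Mobilised children in sampled households, per cluster | c with f = 1 | True 10-point effect becomes |
|---|---|---|---|
| 150 | 4 × 30/150 = 0.80 | 15.3% | 8.5 |
| 200 | 4 × 30/200 = 0.60 | 11.4% | 8.9 |
| 500 | 4 × 30/500 = 0.24 | 4.6% | 9.5 |
| 1000 | 4 × 30/1000 = 0.12 | 2.3% | 9.8 |

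The level moves more than the contrast. At p = 30%, measured care seeking is 0.30 + 0.153 × 0.70 = 40.7% for H = 150, and 0.30 + 0.023 × 0.70 = 31.6% for H = 1000.

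**Step 6, only some interviews later.** With f = 0.5, c halves. For H = 150, c = 7.65% and 10 points become 9.2. For H = 500, c = 2.3% and 10 points become 9.8.

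**Step 7, dependence on who is mobilised.** If mobilisation reached only children who had not otherwise sought care, in equal numbers in every cell, the added events would cancel in the difference-in-differences and only the levels would rise. The attenuation in Step 5 therefore depends on the assumption about who responds.

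**The case against.** Five points can be made for the plan.

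1. **The recall window.** Care seeking is asked for the two weeks before the survey, and mobilisation is on the survey day. Read strictly, a same-day visit is outside the window. This stands for a household interviewed on the day of mobilisation. It does not cover a household interviewed or revisited on a later day, and the protocol does not say whether the window counts back from the interview or from the team's arrival.

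2. **Overlap is not stated.** The protocol assumes one health post per enumeration area. It does not say that a health post serves only that area, or that the four children come from sampled households. This stands, and it is why the size is undetermined.

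3. **Equal design.** The quota is four in both groups at both rounds, and field teams are not told which districts are intervention districts. Difference-in-differences then removes most of an equal inflation. This stands. Masking the teams does not, however, equalise families' response to mobilisation, and acceptance of health-post care is something the intervention sets out to change.

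4. **A large bias might be inferred.** With 100 to 250 households per area and 40% care seeking (both assumed), 4/(100 × 0.65 × 0.30) = 20.5% and 4/(250 × 0.65 × 0.30) = 8.2%. Multiplied by 0.60, these give 12.3 and 4.9 points. A reader might take 5 to 12 points as the bias in the effect. That needs all four children to come from the area, every interview to follow mobilisation, and the contamination to fall in one group or round only. The last condition runs against the equal quota that the protocol plans, so the documents do not support this reading.

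5. **Field-manual detail.** Module order and coding of visits often sit in a fieldwork manual or questionnaire, and neither is shown. That lowers the weight of the point but does not remove it. The protocol itself specifies a procedure that can create outcome events, and the safeguard must be in place before data are collected.

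**Conclusion.** The point holds as a design weakness that is cheap to close. Each link is in the protocol: health-post visits count, the survey prompts such visits at the posts serving the sampled clusters, and nothing separates prompted visits from the outcome.

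The size cannot be determined from the documents. Under the stated assumptions (150 to 1000 households per health post, all interviews after mobilisation, equal contamination in every cell), about 2% to 15% of ill sampled children are affected and a true 10-point effect is measured as 8.5 to 9.8. The loss of 0.2 to 1.5 points compares with a stated detectable difference that starts at 10 points, and it is smaller if only some interviews come later.

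Mild attenuation is the expected effect. A false effect would require response to mobilisation to differ by area and round. That is possible, but no figure in the protocol allows it to be quantified, and nothing in the protocol shows that it happens.

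**What to change.** - State that household interviews in a cluster, including revisits where feasible, are completed before mobilisation starts there, at both rounds.
- As a backstop for late revisits, record the date of each reported visit and whether the survey team prompted it, and do not count prompted visits as care seeking. Treat household-reported treatment received at such visits in the same way.
- If the baseline survey is already done, apply the rule at endline, report the field order used at baseline, and run a sensitivity analysis that treats the two rounds alike. A rule applied at one round only would itself make the rounds differ.

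The cost is slightly less flexible field scheduling and one added date-and-prompt item on the tablet. Sample size and the main analysis do not change.
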